**Figure 2 F2:**
[figure not shown]
Primary outcome measured by optical coherence tomography (OCT). (**A**) Peripapillary retinal fibre layer (RNFL) OCT scan, Spectralis (Heidelberg Engineering), showing the global RNFL thickness. Manual resegmentation is performed as required. Red circle: global RNFL 301 μm. (**B**) Retinal nerve fibre layer scan, Spectralis OCT scan (Heidelberg Engineering), showing the total retinal thickness (TRT), which is measured from internal limiting membrane (red) to Bruch’s membrane (blue). Manual resegmentation is performed as required. Red circle: global TRT 663 μm. G, Global; INF, inferior; N, nasal; NAS, nasal; NI, nasal inferior; NS, nasal superior; SUP, Superior; T, Temporal; TI, temporal inferior; TMP, Temporal; TS, temporal superior.

Secondary outcome measures include global thickness of the RNFL by OCT over 12 and 24 months. Other measures will be evaluated over 6, 12 and 24 months and include alternative OCT optic nerve head measures of papilloedema (total retinal thickness, disc global volume, disc central thickness and disc maximum height) and the OCT measure indicating optic nerve atrophy (macular ganglion cell layer volume) (figure 3).^40^ A trained and certified technician or neuro-ophthalmologist will evaluate each OCT image to confirm scan quality and ensure accurate segmentation before reporting. Other vision outcome measures are visual acuity, measured by logarithm of the minimum angle of resolution units and Humphrey visual field (HVF) PMD. To ensure standardised, high-quality data, the Visual Reading Centre required all sites to undergo training according to a predefined SOP. Site technicians were accredited prior to site initiation. A detailed list of the other secondary outcomes including safety assessments, intervention reporting measures (including complications and revisions), headache outcomes (including monthly headache days (MHD), headache severity (Numerical Rating Scale (NRS) 0–10) and monthly use of acute headache analgesics), patient-reported outcome measures and a health economic evaluation, as well as the exploratory outcomes are included in online supplemental appendix 5.

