### Statistical analysis plan

#### Sample size

There is no established threshold for the minimum clinically important change in RNFL thickness that would define a successful outcome of intervention in patients with IIH.^41^ We analysed optical coherence tomography (OCT) RNFL global thickness in a comparable IIH population undergoing CSF shunting at the Queen Elizabeth Hospital, Birmingham, UK between 2019 and 2021. The cross-sectional SD was 128 µm (OCT RNFL global thickness pre-intervention: 364 µm) and data from logistical regression models illustrated values of 253.9 µm at 2 weeks, 202.6 µm at 1 month, 90.0 µm at 3 months and 87.2 µm at 6 months post-intervention.^42^

Using a conservative correlation between within-subject serial measurements (rho, ρ) of 0.5 and a minimally clinically important difference in global RNFL of 70 µm, it was estimated that this trial could show a potential benefit of an intervention with a sample size of 66 patients, each providing a complete dataset of all indices across all scheduled follow-up visits.

As this trial is longitudinal, we expect that some participants will withdraw from the study or fail to complete a visit, leading to <100% data collection for the primary outcome. In the two arms of a historical IIH trial,^43
44^ the proportion of missing data was 6.5% and 6.7%. Therefore, we expect missing data in approximately 6.6% of values; 95% CIs using Wilson’s method are 2.6% to 15.7%. For our sample size estimation, we use the upper limit of this and increase the number of complete case series by 16%.

We plan to use hierarchical models to longitudinally analyse OCT. Therefore, the methods of Diggle *et al*^45^ are used to derive the sample size. With assessments at trial entry (days −14 to 0), weeks 1 and 2 and months 1, 2, 3, 4 and 6, and in line with the values given above, a minimum of 40 participants per arm are required; at least 80 participants in total.

As noted in figure 1, online supplemental appendix 1 and in the ‘Discussion’ section, sites have the option to perform two of three early visits (at months 2, 3 and 4) virtually, whereby ophthalmology data would not be collected. If two visits are virtual then the power estimate for the trial’s primary outcome is 84%. However, we anticipate our power to be higher than this (either close to or >90%) as:

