Other visual outcomes will be analysed in a similar way as they can be assumed to be continuous. For the analysis of global RNFL thickness, we acknowledge that loss of the ganglion cell layer (GCL) may cause a pseudo-reduction in RNFL. Therefore, in addition to the primary estimand detailed above, we aim to differentiate any reduction in RNFL owing to an improvement in disease following intervention from any reduction in RNFL owing to the loss of GCL. Therefore, we propose a supplementary estimand, which will be analogous to the analysis detailed above, with the key difference being that GCL will also be adjusted for through the joint modelling of both. This analysis will have the added benefit of allowing the ascertainment of whether the rate of GCL death is comparable between arms.

The major attributable complication rate between the DVSS and CSF shunting arms will be compared using a two-sample test for a difference in proportions.

Headache outcomes, including MHD will be analysed using multilevel negative binomial models with constant overdispersion parameter. These models will have fixed terms for the mean baseline value, the assessment times and treatment arm, with random intercepts to reflect the heterogeneity in baseline values and the serial correlation in repeated measures. Akin to the primary outcome, the presence of a treatment effect will again be tested by a likelihood ratio test against a nested model with no treatment variable and otherwise identical model specification.

All other outcomes, their intercurrent events of interest and estimands are given in the SAP.

Supplementary subgroup analyses may be performed by shunt type (LP vs VP CSF shunt) against DVSS, as appropriate.

There are no formal interim analyses with associated decision criteria. Instead, the independent data monitoring committee (DMC) will meet at least annually, and be presented with interim analyses, including safety and primary outcome data.^41^

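### The negative binomial model named for all headache outcomes does not suit the 0–10 severity score and ignores the upper limit of monthly headache days

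*Protocol article*

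**What the plan says.** The Outcome analyses section of the protocol article names one model family for this group of outcomes: "Headache outcomes, including MHD will be analysed using multilevel negative binomial models with constant overdispersion parameter". It then gives the structure: "These models will have fixed terms for the mean baseline value, the assessment times and treatment arm". Participant-level random intercepts are added to capture baseline differences between people and the dependence among their repeated values. For inference, "the presence of a treatment effect will again be tested by a likelihood ratio test against a nested model with no treatment variable".

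The Trial outcomes section says what the group contains. Besides monthly headache days, it lists "headache severity (Numerical Rating Scale (NRS) 0–10) and monthly use of acute headache analgesics". The Outcome analyses section exempts none of these three from the negative binomial model. Only the outcomes outside the groups already described are referred to the SAP for their analysis.

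**The concern.** A negative binomial is a model for event counts with no upper limit. Its variance is at least its mean and grows as the mean grows. Two of the three headache outcomes do not behave that way.

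- **Severity.** A 0–10 rating counts nothing and cannot exceed 10. Its variance may well be smaller than its mean. The natural output of the model, a ratio of expected counts, has no clear meaning for a rating.
- **Monthly headache days.** These are counts, but they stop at 28 to 31. Near that limit the variance shrinks, whereas the model's variance keeps rising.

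At stake are the fit of the model, the meaning of the reported effect and possibly the efficiency of the test, for secondary outcomes that the abstract names. The article itself treats boundedness as a modelling difficulty when it explains why perimetric mean deviation was dropped as primary outcome (Discussion, Change in primary outcome). The same reasoning applies to these two outcomes.

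**Working it through.** The article states no mean, SD, effect size or power for any headache outcome, so there is no figure of the plan to reproduce. From the article come the model, the likelihood ratio test, 1:1 allocation and the trial size ("a minimum of 40 participants per arm are required; at least 80 participants in total"). Everything else below is assumed.

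**1. Variance limit.** For a negative binomial with mean μ and overdispersion α ≥ 0, variance = μ + αμ² ≥ μ. With μ = 6, the smallest possible SD is √6 = 2.45. A score with mean 6 and SD 2 (assumed) has variance 4, below 6. A random intercept can only add variance, so it does not help.

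**2. Mass above the limit of a month.** Matching mean and SD gives the size parameter k = μ²/(SD² − μ).

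| Assumed mean, SD | k | P(>28 days) | P(>31 days) |
|---|---|---|---|
| 20, 8 | 400/(64 − 20) = 9.09 | 14.3% | 8.6% |
| 24, 7 | 576/(49 − 24) = 23.04 | 24.6% | 14.2% |

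**3. Fit of a random-intercept negative binomial to bounded data.** This used 500 simulated trials per scenario, 40 per arm, 5 post-baseline visits, a 28-day limit and a two-sided 5% test. The fitted mass beyond the limit was:

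- Headache days: 25–28% at control mean about 23 (39% of control values at the limit), 11–13% at mean 17, and 7–9% at mean 12.
- Severity: 3–4% above 10.

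Within-person variance was about 2.3 against a mean of 5.0 for severity, and about 7 against 23 for headache days with a strong ceiling. In both cases the overdispersion estimate fell to its lower limit. At a mean of 12 days it did not (about 0.05), so the misfit for headache days depends on how close participants are to the ceiling.

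**4. Power in the same simulations (%).** The linear comparator is a baseline-adjusted analysis of participant means. The bounded-scale comparator is the same analysis after an empirical logit.

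| Scenario (control mean) | Negative binomial | Linear | Bounded scale | Rank |
|---|---|---|---|---|
| Days, 23 | 91.8 | 92.0 | 94.6 | 85.0 |
| Days, 17 | 83.6 | 85.0 | 88.0 | 87.0 |
| Days, 12 | 83.4 | 84.8 | 88.2 | 87.6 |
| Severity, 5.0 | 80.2 | 82.0 | 81.0 | 78.2 |
| Severity, 4.1 | 80.2 | 82.4 | 83.0 | 80.0 |

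- Loss against linear: 0.2, 1.4 and 1.4 points for days; 1.8 and 2.2 for severity.
- Loss against the bounded scale: 2.8, 4.4 and 4.8 points for days; 0.8 and 2.8 for severity.
- Against the rank analysis, the negative binomial ranged from 4.2 points worse (87.6 − 83.4) to 6.8 points better (91.8 − 85.0).

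**5. Type I error.** The negative binomial gave 5.0–7.0% and the comparators 4.8–7.0%, with a Monte Carlo standard error of about 1 point.

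**6. Sensitivity to the assumptions.**

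- A second set of fits (400 trials per scenario, baseline-adjusted, visit terms omitted) gave 72.5–77.5% against 75.2–76.2% for a linear analysis of severity, and 73–79% against 78–85% for headache days, with no clear loss of size control.
- A third set for headache days, with 6 visits and 19–31% of values at the ceiling, gave 68–76% against 75–81% for a linear analysis.
- For headache days, the ends of these ranges lie 5–7 points apart, at or slightly above the top of the range in step 4. Each power estimate from 400 trials has a standard error of about √(0.75 × 0.25/400) = 2.2 points.

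**The case against.** The article is a condensed account. It introduces its analysis text as brief and refers to a predefined SAP for detail. The full outcome list is in a supplementary appendix that is not shown, so the SAP may already give severity its own model or include a check of fit. The absence of a fallback model for headache in the article, where one is given for the RNFL model, is therefore not evidence that none exists. This stands as a caution. It does not remove the point, because the article states a model for headache outcomes without exception and does not leave the choice open.

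A reader might infer that the misfit makes the treatment test invalid or costs the trial material power. The documents do not support that. They give no headache distribution from which a loss could be calculated. In the assumed scenarios the size was close to that of the alternatives and the power differences were small. Probability placed on impossible values shows poor distributional fit. It does not by itself show a wrong comparison between arms.

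For headache days, a ratio of mean days is well defined even when the outcome is bounded, and choosing a beta-binomial over a negative binomial is partly a matter of preference. The gain from a multilevel beta-binomial over the planned model has not been shown here; the bounded comparator was a logit-scale analysis of means. If analgesic use is recorded as doses, it is a count with no fixed ceiling and the negative binomial is a natural choice. All of this stands, and it leaves the severity score as the firm core.

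**Conclusion.** The point holds in a limited form. As written, the article assigns an unbounded count model to a bounded rating that is not a count, and it ignores the upper limit on monthly headache days. For severity this is a clear mismatch: the model cannot represent a variance below the mean, and a ratio is a poor summary of a rating. For headache days the mismatch depends on how many participants are near the ceiling, which the documents do not say.

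The effect on inference appears small: roughly nominal size, and a power loss of about 0–3 points for severity and about 0–5 points for headache days, perhaps slightly more when many values sit at the ceiling. These figures rest on assumed means, spreads, effects and visit numbers. The outcomes are secondary and the sample size does not depend on them. The change is worth making for fit and interpretability, not to recover power.

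**What to change.** Name a model for each headache outcome.

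- **Severity (0–10):** a linear mixed model, or an ordinal mixed model, with the same baseline, visit and arm terms. Report a difference in points where the linear model is used.
- **Monthly headache days:** a model that respects the upper bound, such as a multilevel beta-binomial with the days in the period as denominator, or a linear mixed model. Report a difference in days and keep the negative binomial as a sensitivity analysis.
- **Analgesic use:** keep the negative binomial if it is recorded as doses; if it is recorded as days, treat it like headache days.

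If the SAP already separates severity from the counts, it is enough to align the article's sentence with it. The cost is SAP wording and model code, plus a less familiar model for headache days if the beta-binomial is chosen. No data collection changes. The Trial status section expects recruitment to run until 28 February 2027, so the change can still be prespecified.

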#### Economic evaluation

To assess the cost-effectiveness of DVSS compared with CSF shunting, a within-trial economic evaluation will be undertaken and will include both a cost-effectiveness analysis and a cost-utility analysis at 12 months. If the economic evaluation at 12 months reveals that DVSS is not dominated by CSF shunting (ie, it is not both more costly and less effective) then a decision-analytic model will be developed to enable an economic analysis over a longer time horizon. The model will be populated using trial data collected at 24 months, as well as data from other sources to extrapolate results over a lifetime horizon. The economic evaluation will be undertaken from a UK health system perspective.

For the cost-utility analysis, quality-adjusted life years (QALYs) will be measured using the EQ-5D-5L collected at baseline, 1 and 2 weeks immediately following the intervention and then at 1, 4, 6 and 12 months and at any unscheduled visit for revision/device failure.

Utility weights will be obtained by using the EQ-5D index tariff. Mean differences in EQ-5D between the trial arms will be estimated and presented with statistical tests of significance. Any imbalance in baseline utility will be adjusted. The within-trial cost-effectiveness analysis will use ‘major complications avoided’ as the outcome measure, assessed using the Clavien-Dindo grade III–V criteria for classification.^47^

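### Adjustment for baseline utility is tied to imbalance with no trigger stated; it should be pre-specified whatever the observed balance

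*Protocol article*

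**What the plan says.** The protocol article, Economic evaluation, plans a within-trial cost-utility analysis at 12 months in which "quality-adjusted life years (QALYs) will be measured using the EQ-5D-5L collected at baseline" and at later visits up to 12 months. On the comparison it says "Mean differences in EQ-5D between the trial arms will be estimated and presented with statistical tests of significance", and then "Any imbalance in baseline utility will be adjusted". It does not say what counts as imbalance, what method is used, what is reported when the arms look balanced, or whether the adjustment carries through to QALYs.

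The Outcome analyses section treats covariates differently. The RNFL models adjust for the stratification variables as a matter of course. For the headache models it says "These models will have fixed terms for the mean baseline value, the assessment times and treatment arm". Neither depends on how the arms turn out to compare.

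The number of participants comes from the RNFL calculation in Sample size: "a minimum of 40 participants per arm are required; at least 80 participants in total". The economic section states no sample size, power, EQ-5D standard deviation or EQ-5D correlation of its own.

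**The concern.** Two competent analysts could follow this text and report different results. One would adjust always, since some difference in mean baseline utility is practically certain. The other would inspect the baseline table, judge the arms similar, and report the unadjusted difference. Under the second approach the data choose the estimator, in an open-label trial.

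Imbalance is also the wrong criterion. Adjustment helps because baseline utility explains part of the spread in later utility, and it does so whether or not the arms look alike. Baseline utility also enters the QALY calculation itself.

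What is at stake is the precision and reproducibility of the utility comparison, which has about 40 participants per arm and was not sized for that purpose. The 12-month economic result also decides whether a longer-term model is built.

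**Working it through.** **Plan's own figure.** The economic section has no figure to reproduce. The only input borrowed from the plan is 40 per arm, which comes from the RNFL calculation: "with a sample size of 66 patients, each providing a complete dataset of all indices", "The cross-sectional SD was 128 µm", and "rho, ρ) of 0.5 and a minimally clinically important difference in global RNFL of 70 µm". The repeated-measures formula is n per arm = 2(z_α + z_β)²σ²[1 + (k−1)ρ]/(kδ²). With k = 8 assessments, 90% power and one-sided 5% (the error rate is not stated in the article, so these are assumptions), n = 2 × 8.56 × 128² × 0.5625/70² = 32.2. That gives 33 per arm, or 66. Allowing for 16% loss, 66/0.84 = 78.6, hence 80 in equal arms. The correlation of 0.5 used there is between RNFL measurements and says nothing about EQ-5D.

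**Chance imbalance.** With 40 per arm, the standardised baseline difference (SMD) has standard error √(2/40) = 0.224.
- Expected absolute SMD: 0.224 × √(2/π) = 0.18.
- Probability that it exceeds 0.1: 0.66. Probability that it exceeds 0.2: 0.37.
- The adjusted and unadjusted estimates differ by about r × SMD. At an assumed r of 0.5 and the expected SMD, that is 0.5 × 0.18 = 0.09 SD.

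**Always against never adjusting.** The variance factor is about 1 − r², where r is the assumed correlation between baseline and follow-up utility.

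| Assumed r | Variance factor | Standard error | 80 patients worth |
|---|---|---|---|
| 0.3 | 0.91 | −4.6% | 80/0.91 = 88 |
| 0.5 | 0.75 | −13.4% | 80/0.75 = 107 |
| 0.7 | 0.51 | −28.6% | 80/0.51 = 157 |

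**Conditional adjustment.** None of the triggers below is in the documents; they span what an analyst might do. The results are simulated with 40 per arm, 40,000 runs and r = 0.5. Variance is relative to the unadjusted theoretical value. Power is for an assumed true difference of 0.5 SD at two-sided 5%.

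| Rule | Relative variance | Power | Type I error |
|---|---|---|---|
| Adjust only if baseline p<0.05 | 0.92 | 60% | 4.3% |
| Adjust only if absolute SMD > 0.2 | 0.79 | 64% | 3.7% |
| Adjust only if absolute SMD > 0.1 | 0.75 | 67% | 4.2% |
| Always adjust | 0.75 | 71% | 5% (nominal) |

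The simulated variance without adjustment was 0.99. The p<0.05 rule therefore loses (0.92 − 0.75)/(0.99 − 0.75), about 70% of the available gain. The SMD > 0.1 rule loses almost none of the gain in the point estimate, because the two estimates nearly coincide when the baseline difference is small. It still loses some power, because the wider unadjusted standard error is reported whenever the trigger is not met. That mismatch also makes the conditional tests conservative.

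**QALYs.** The simulation covers one follow-up utility, not a QALY. If QALYs are areas under straight lines between visits (an assumption), the first interval is one week. Baseline then has a direct weight of ½ × 1/52 = 0.0096 of a year, about 1% of the 12-month total. Its direct entry into the QALY is small, so the correlation with later utility matters more.

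**The case against.** The strongest reply is that the words 'only if' do not appear. No balance test or threshold is given, and nothing says that an unadjusted estimate will be reported otherwise. Read literally, any imbalance means any non-zero difference, so adjustment would occur in practically every realised trial and the loss would be zero. This stands. A reader might infer that the plan tests utility unadjusted and adjusts only after a significant baseline difference, but the text does not say so. The p<0.05 figures are the far end of a range, not a description of the plan.

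A reader might also infer a false-positive problem. The figures show the opposite: the conditional rules fall slightly below 5%.

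It can further be said that a condensed article leaves regression detail to the SAP, which is not shown and may already specify unconditional adjustment. That is fair, and missing detail is not the complaint. The complaint is that the article does state a ground for adjustment, and the ground is imbalance, while its RNFL and headache models carry their covariates unconditionally. No text shown commits to the same for utility.

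Finally, the rule for building the longer-term model asks whether stenting is dominated and is not stated as a significance test. The power figures therefore do not translate directly into that decision.

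**Conclusion.** The point holds as a minor one. The sentence gives imbalance as the only reason to adjust and sets no trigger, so it permits a data-dependent choice of estimator where a fixed rule is available from data already scheduled for collection.

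Its size cannot be fixed from the documents. It depends on an EQ-5D correlation, a trigger and, for power, an effect size, none of which they give. Depending on how the sentence is followed, the cost lies between nothing and most of the precision that baseline adjustment offers. A reader might take the point to weaken the primary comparison or the target of 80 participants. It does neither, since both rest on RNFL and its own model.

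**What to change.** Replace the sentence in Economic evaluation with: *Between-arm differences in EQ-5D and QALYs will be estimated by regression adjusted for baseline utility (and the minimisation factors), regardless of observed balance.* Use that adjusted estimate in the cost-utility result, so that the reported utility difference and the economic conclusion rest on the same analysis. Including the minimisation factors is for consistency with the RNFL models; the argument about baseline utility does not depend on it.

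The cost is one sentence and no new data, since EQ-5D is already scheduled at baseline. Participants without a baseline value will need a stated rule if the SAP does not already have one. If the SAP already adjusts unconditionally, the change only brings the article into line with it.
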